## 6. Trial Steering Committee

### *Define function of committee and list names etc*

This committee will comprise of CI ([name]), at-least two of other co-applicants (Drs [name], [name] and [name]), research nurse (TBA), research assistant/s ([name], [name] and TBA) and trial statistician ([name]). The committee will meet regularly to monitor recruitment and completion of study objectives with formal meetings annually to monitor the data quality, safety and achievement of study objectives.

## 7. Direct Access to Source Data and Documents

*The sponsor should ensure that it is specified in the protocol (or reference is made to another written agreement) that the investigator(s) and the institution(s) will permit trial-related monitoring, audits, REC review, and regulatory inspections (where appropriate) by providing direct access to source data and other documents (ie patients' case sheets, blood test reports, X-ray reports, histology reports etc).*

## 8. Ethics & Regulatory Approvals

*A statement that the trial will be conducted in compliance with the principles of the Declaration of Helsinki (specifying which amendment), the principles of GCP and any applicable regulatory requirements (specify current legislation) is essential. State the name and address of the REC to which the study protocol and other documentation will be submitted (eg Liverpool Adult Research Ethics Committee or Liverpool Children's Research Ethics Committee). You should also state that any subsequent protocol amendments will submitted to the REC, and that you provide the REC with progress reports, and a copy of the Final Study Report*

This clinical trial will be conducted in accordance with the ethical principles as per the Declaration of Helsinki, and the principles of Good Clinical Practice and all applicable requirements as stated in the R&D approval. The Ethics for this study have been approved by the NRES Committee London – Westminster (REC reference 10/H0802/13).

Any subsequent protocol amendments will be submitted to the REC and progress reports and copy of final study report will be provided to REC as per standard requirements.

## 9. Quality Assurance, Data Handling, Publication Policy and Finance

*Give details as to how QC will be maintained, data handling procedures, publication policy and finance.*

### **Analysis:**

- (i) [name], Professor of Medical Statistics, King's College London and her team will provide high level statistical input to the trial, overseeing the randomisation and formulating the analysis plan. Differences in outcome will be compared by a random effects (mixed) model. [name] will formulate a detailed analysis plan during the work-up phase of the study.
- (ii) Interim analysis to be performed at 1-year by statistical team to check if SD of measured indexed LV mass (LVMI) is in keeping with initial projections.
- (iii) Appointment of 'Drug monitoring committee' (DMC). The members of this committee will include independent observers as per routine standards. The DMC will review the results of the proposed interim analysis at 1-year following commencement of study.

- (iv) Interim analysis will also review data regarding the safety of proposed study arms at 1-year. The results will be reviewed by DMC and used to inform REC and the wider research team.

**Data handling:**

- (i) Data will be entered on an online data entry platform 'MedSciNet'. This will be overseen by [name], at the Biomedical Research Centre at King's Health Partners and [name]. [name] will also help with the safe running of study database and collation of results.
- (ii) The following research team members will be 'blinded' to the blood pressure percentile of the patient.
  - a. All technologist/s performing the cardiac and vascular measurements
  - b. Research team member entering data to MedSciNet
- (iii) The clinical team will also be kept blinded to the results of the echocardiogram and vascular studies.

**Statistical Analysis Plan**

## A) QUANTITATIVE ANALYSIS PLAN

### 1. Description of the trial

#### 1.1 *Principal research objectives to be addressed*

This study will determine whether controlling blood pressure to a lower level than is currently recommended will prevent the damage to arteries and heart.

##### Primary objectives

Perform a randomised controlled trial to determine whether aggressive blood pressure reduction (below the 40th percentile) compared to standard care (between the 50th-75th percentiles) is effective in normalising left ventricular mass.

##### Secondary objectives

Secondary objectives will be to examine the effects of aggressive versus standard blood pressure reduction on relative wall thickness and progression of renal failure.

#### 1.2 *Trial design including blinding*

Interventional multi-centre RCT UK-wide national trial with a sample size of 144 patients.

The following research team members will be 'blinded' to the blood pressure percentile of the patient: (i) technologist/s performing the cardiac and vascular measurements and (ii) Research team member entering data to MedSciNet. The clinical team will also be kept blinded to the results of the echocardiogram findings.

### **1.3 Eligibility Criteria**

#### Inclusion criteria

- i. aged 2 to 15 years with
- ii. chronic kidney disease with stages 1-4 in the last 12 months and
- iii. with or without anti-hypertensive/s medications (irrespective of recent change/s in antihypertensive therapy). Subjects on anti-hypertensive medications must be able to tolerate either an ACEi or ARB's.

#### Exclusion criteria

- i. age <2 and >15 years
- ii. subjects who have/had an arterio-venous fistulae,
- iii. subjects who have/had are on dialysis
- iv. subjects who have/had a functioning kidney transplant
- v. patients with symptomatic BP or with past history of difficulty to control BP or
- vi. patients in whom there is a clinical urgency to treat BP and inclusion in study may result in possible delay of treatment
- vii. patients with arrhythmia or clinical heart failure
- viii. patients with known structural cardiac abnormality
- ix. subjects on treatment with angiotensin converting enzyme inhibitor (ACEi) or angiotensin receptor blocker (ARB) agents for treatment of proteinuria only or
- x. subjects who are likely to be of clinical concern following up or down titration of BP levels as described in 'Appendix 3'
- xi. subjects who are unable or intolerant to performance of study measurements e.g. height, echo or PWV
- xii. subjects who have/had intolerance to Angiotensin converting enzyme inhibitors (ACEi) and ARB's drug/s or have any existing contraindications

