a) Clinic blood pressure will be taken as the mean of 3 measurements using the appropriate sized cuff and a calibrated aneroid instrument according to current guidelines. All observers will undergo appropriate training including the evaluation of their variation from independent experienced investigators. Normative criteria will be those defined in the Fourth report of the National High Blood Pressure Education Program Working Group in the United States ('Fourth report') [32] and will be expressed as z-scores.

b) 24-hour ABPM studies will be performed in patients > 5 years and > 120 cm using Spacelabs 90217 oscillometric ABP devices (Spacelabs Inc, Redmond, Wash, USA). The performance of 24-hour ABPM is not mandatory. Measurements will be performed once every 30-minute throughout the period of monitoring. Daytime and nighttime periods during each ABP recording will be defined using information in the patient 'ABPM diary card'. An ABPM study will be judged to be of poor quality and excluded if (1) if there are more than 3-hours of interrupted recordings at any time during the 24-hour period; (2) if the duration of ABPM recording is inadequate and less than 20-hours in total, less than 12-hours continuously or does not include any nighttime measurements. All mean ABPM parameters will be analysed as z-scores using the normative limits as per *Wuhl et al* [38]. Nocturnal systolic and diastolic dipping status will be defined as a reduction in nighttime systolic (or diastolic BP) of greater than 10% of the daytime systolic (or diastolic) BP. All ABPM studies will be analysed centrally at the ECH.

(v) Central blood pressure

Central blood pressure will be estimated from radial tonometry and modified BP measurement using Centron™ BP machine. We are currently performing a validation study to determine which method is most reliable.

(vi) Echocardiography

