High resolution ultrasound (Linear transducer for iE33 (15-6MHz) will be used to obtain images of the common carotid artery. Mean common carotid intima-media thickness (cIMT) will be assessed using automated software (Medical Imaging Applications LLC, Iowa, USA) from digitized images obtained in diastole of the near and far walls of the both common carotid arteries 1-2 cm proximal to the flow divider [45,46]. This method is recognized as one of the most robust measures of IMT since the

reproducibility of common carotid IMT measurements is higher than that of other segments [47], and in most studies to date additional measurements from the bifurcation and internal carotid have not improved the predictive value of IMT [48,49].

(viii) Arterial stiffness

Arterial stiffness will be determined by measuring carotid-femoral pulse wave velocity (PWV) in children able to co-operate with this measurement and by measuring arm-thigh PWV in all subjects. Carotid-femoral PWV will be determined using the SphygmoCor system (Atcor medical, Australia) in which ECG referenced sequential carotid and femoral applanation tonometry is performed. This is usually well tolerated in children but some children are unable to keep still during carotid tonometry. An alternative technique (Vicorder, Skidmore Medical) employs simultaneous measurement of pulse waveforms from pressure cuffs placed around the arm and thigh. This method is particularly well tolerated in children. Although it is not an accepted standard we have shown that it is highly (correlation coefficient 0.7) correlated with carotid-femoral PWV obtained using the SphygmoCor system.

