## **3.3 Withdrawal of Subjects**

*Please provide details of when and how to withdraw subjects from the trial or investigational product treatment. It is essential that you specify the type and timing of the data to be collected for withdrawn subjects and indicate whether (and if so, how) withdrawn subjects are to be replaced, as well as arrangements for safety assessment follow-up of any subjects withdrawn from the trial as a result of (Serious) Adverse Events.*

- i. Subjects will be withdrawn if they are unable to tolerate the performance of study related measurements e.g. height, echo or PWV or if they develop concerning adverse effects as a result of ACEi/ ARB's class of anti-hypertensive drug/s used as part of taking part in the study.
- ii. If a subject wishes to withdraw from the study this will be allowed. Identifiable data already collected with consent would be retained and used in the study. No further data or tissue would be collected or any other research procedures carried out on or in relation to the participant.

- iii. In principle we would aim to keep blood and urine specimen and data gathered up to the point that the consent is lost. However as the patients are continually followed up by the clinical team we will be able to determine if the patient wants us to withdraw their data from the study. We will always follow the patient and/or their families wishes.

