#### Patient withdrawal

- i. Subjects will be withdrawn if they are unable to tolerate the performance of study related measurements or if they develop concerning adverse effects as a result of ACEi/ ARB's class of anti-hypertensive drug/s used as part of taking part in the study.
- ii. If a subject wishes to withdraw from the study this will be allowed. Identifiable data already collected with consent would be retained and used in the study. No further

data or tissue would be collected or any other research procedures carried out on or in relation to the participant.

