### **2.5 Descriptive statistics for outcome measures**

#### Primary endpoints

The primary endpoint of the RCT is to evaluate the benefit of intensive blood pressure control on the normalization/ limitation of cardiovascular target organ damage as assessed by LV mass index. The principal outcome measure will be the change in LV mass index from baseline in each treatment arm for each year of follow-up.

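### Withdrawal rule (i) removes randomised children who cannot tolerate a non-primary test such as PWV, and no section keeps their echo follow-up for LVMI

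*Combined protocol and SAP*

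**What the plan says.** - **Withdrawal.** Protocol section 3.3, item i (repeated in the trial supplement placed before the protocol): "Subjects will be withdrawn if they are unable to tolerate the performance of study related measurements e.g. height, echo or PWV". SAP section 1.3, Patient withdrawal, item i, omits the examples: "Subjects will be withdrawn if they are unable to tolerate the performance of study related measurements or if they develop concerning adverse effects".
- **Voluntary withdrawal.** Item ii of the same lists begins "If a subject wishes to withdraw from the study this will be allowed" and goes on to stop all further data collection. That stop is written under item ii and not under item i.
- **Entry.** Exclusion xi, in protocol section 3.2, the supplement and SAP section 1.3, bars "subjects who are unable or intolerant to performance of study measurements e.g. height, echo or PWV".
- **Primary outcome.** SAP section 2.5: "The principal outcome measure will be the change in LV mass index from baseline in each treatment arm for each year of follow-up". SAP section 1.7 defines LVMI as echo-derived LV mass divided by height to the power 2.7.
- **Status of PWV.** It is a secondary endpoint in the protocol synopsis. SAP section 2.5 names only relative wall thickness as secondary, although SAP Table 1 still schedules PWV.
- **Analysis.** SAP section 3 sets intention to treat. Protocol section 2.4.1 and SAP section 1.9 choose a mixed model partly because it tolerates missing measurements. SAP section 3.1.1 assumes that data missing after withdrawal are missing at random.
- **Contrast.** Under Subjects in the protocol's design and methods section, children who start dialysis or receive a transplant leave the randomised comparison but are still measured until the study ends.

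**The concern.** The rule puts PWV on the same footing as height and echocardiography, although only the last two are needed for the primary outcome. As written, failing a non-primary test after randomisation is enough to remove a child, and nothing says that the yearly echo continues. A child withdrawn at year 1 would lose the year 2 and year 3 echoes that SAP Table 1 schedules.

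The plan itself would create this missing LVMI, and it could be avoided. Intention to treat is meant to keep every randomised child's outcome in the comparison, and the mixed model was chosen to cope with gaps. Neither helps if the child's primary measurement stops because a different measurement could not be made. The gap is then covered only by the missing-at-random assumption, and the one sensitivity analysis in SAP section 3.1.4 relaxes linearity over time, not that assumption.

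**Working it through.** **1. What the primary outcome needs.** LVMI = LV mass / height^2.7. The inputs are the echo and height. PWV, carotid intima-media thickness (cIMT), central pressure, blood and urine do not enter.

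**2. What happens to each kind of leaver.**
- Starts dialysis or receives a transplant: leaves the randomised comparison, measurements continue (stated).
- Chooses to withdraw (item ii): no further data (stated).
- Withdrawn for not tolerating a measurement (item i): continuation of echo is not stated.

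Table S3 lists reasons for stopping further follow-up. It includes ACEi/ARB intolerance (6 intensive, 3 standard), which is the other ground in item i. So withdrawals under item i were reported as ending follow-up.

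**3. How often it could have happened (Table S3).**
- Intensive: 2 + 6 + 7 + 3 = 18 of 64.
- Standard: 0 + 3 + 4 + 3 = 10 of 60.
- Total: 28 of 124. No row gives intolerance of PWV or of any other measurement.
- Cause not known: 1 + 2 = 3, and 3/124 = 2.4%. This is taken as the upper limit.

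**4. What that is worth in power.** Inputs from protocol section 2.4.1 and SAP section 1.8: n = 60 per arm, difference 3.1 g/m^2.7, SD of change 6 g/m^2.7, P<0.05, stated power 90%.

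Power = Φ( δ / (SD·√(2/n)) − z )

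- Standard error: 6 × √(2/60) = 1.095, and 3.1 / 1.095 = 2.830.
- Two-sided: 2.830 − 1.960 = 0.870, power 80.8%.
- One-sided: 2.830 − 1.645 = 1.185, power 88.2%.

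The stated 90% is not reproduced two-sided, which is the reading that the planned 95% CI implies. That is a separate matter; 80.8% serves here as the baseline.

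With 2.4% of children lost:
- n = 60 × (1 − 0.0242) = 58.5 per arm.
- Standard error: 6 × √(2/58.5) = 1.109, and 3.1 / 1.109 = 2.795.
- 2.795 − 1.960 = 0.835, power 79.8%.

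The loss is 80.8 − 79.8 = 1.0 point at most, and 0 if none of the three was due to this rule. The documents give no rate of PWV intolerance. Under a purely assumed loss of 5% or 10% of randomised children, the same formula gives 78.8% and 76.6%, but Table S3 leaves no room for losses of that size (5% of 124 is about 6 children).

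**The case against.** **PWV has a purpose in the protocol.** Arterial stiffness appears in primary objective 1, arterial structure and function in primary objective 2, and PWV has its own detectable difference in section 2.4.1. Requiring children to manage it at entry is therefore partly a design choice. That stands for exclusion xi. It does not explain why a child already randomised should lose echo follow-up when PWV fails.

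**The documents do not state that echo stops.** This is right as to the text: the stop on data collection belongs to item ii. Table S3 points the other way, though not conclusively. It also lists eGFR below 15, and some of those children may have been measured further under the dialysis and transplant provision. The silence is itself the defect.

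A reader might infer more than the documents support:
- *That exclusion xi loses primary-endpoint data.* Baseline tests precede randomisation, so a child excluded there never contributes LVMI. The effect is on recruitment and generalisability.
- *That the standard error is inflated by a set percentage through exclusions at entry.* That needs an intolerance rate, which is not given, and assumes that excluded children are not replaced by further screening.
- *That the rule contradicts the PWV methods.* The protocol says of carotid-femoral PWV: "This is usually well tolerated in children but some children are unable to keep still during carotid tonometry". But it plans arm-thigh PWV for every child and describes that method as very well tolerated, so failing tonometry need not mean failing PWV. This also limits how often the rule would apply.
- *That it contradicts the ambulatory monitoring text.* "The performance of 24-hour ABPM is not mandatory" concerns a different measurement.
- *That the SAP rule is wider.* The protocol's list is only of examples, so it was already open-ended.
- *That the loss falls on the youngest children.* No figures by age are given.

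**Conclusion.** The point holds for the withdrawal rule after randomisation. As written, a randomised child must leave for failing a measurement that LVMI does not use, and the plan does not preserve that child's echo, although it does so for children who start dialysis or receive a transplant. This works against intention to treat and leaves an avoidable loss to the missing-at-random assumption.

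The shown effect is small: none of the 28 withdrawals is attributed to this cause, and the ceiling is about 1 power point. That ceiling assumes that all 3 unknown-cause withdrawals arose from the rule, that these children would otherwise have supplied endpoint LVMI, and that the plan's two-group calculation is a fair stand-in for the mixed model. The case for changing the text rests on the rule being needless and cheap to correct, not on demonstrated harm to the result.

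Exclusion xi is a secondary matter. The SAP keeps PWV there while no longer listing it as an endpoint, and the two should be reconciled.

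**What to change.** 1. In withdrawal rule (i), in the supplement, protocol section 3.3 and SAP section 1.3, limit the measurement ground to inability to obtain height or echocardiography. The adverse-effects ground in the same item is not part of this point.
2. Add that a child who cannot do PWV, cIMT or another non-primary measurement stays in the trial, with that value recorded as missing, annual echo continued, and LVMI analysed in the allocated arm.
3. Reconcile exclusion xi with the SAP's endpoint list: either drop PWV from the named measurements or state why it is still required at entry.

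The cost is a change of wording and some missing secondary values, which the mixed model is meant to handle. SAP section 1.5 describes randomisation in the past tense, so changing exclusion xi now would not alter who entered; items 1 and 2 matter for any child still under follow-up.

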#### Patient withdrawal

- i. Subjects will be withdrawn if they are unable to tolerate the performance of study related measurements or if they develop concerning adverse effects as a result of ACEi/ ARB's class of anti-hypertensive drug/s used as part of taking part in the study.
- ii. If a subject wishes to withdraw from the study this will be allowed. Identifiable data already collected with consent would be retained and used in the study. No further

data or tissue would be collected or any other research procedures carried out on or in relation to the participant.

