| Eccentric LVH n (%)           | 4 (6)                          | 5 (8)                         |
| Concentric LVH n (%)          | 0 (0)                          | 0 (0)                         |

LVEDd, left ventricular end diastolic diameter; LVESd, left ventricular end systolic diameter; IVS, inter-ventricular septum; PW, posterior wall; RWT, relative wall thickness; LVH, left ventricular hypertrophy; LVM, left ventricular mass; LVMI, indexed left ventricular mass.

**Table S3:** Details of reasons for stopping further follow up of eligible randomly assigned study participants in the HOT-KID trial intention to treat population.

|                                                       | Intensive arm
(n=64) | Standard arm
(n=60) | P       |
|-------------------------------------------------------|-------------------------|------------------------|---------|
|                                                       | (A)                     | (B)                    | A vs. B |
| Withdrawn or elected to withdraw from trial           | 18 (28)                 | 10 (17)                | 0.13    |
| (i) Unable to reach BP target despite multiple agents | 2 (3)                   | 0                      |         |
| (ii) ACEi/ARB intolerance                             | 6 (9)                   | 3 (5)                  | 0.36    |
| reduction in glomerular function rate                 | 5                       | 2                      |         |
| dizzy                                                 | 0                       | 1                      |         |
| leg pains                                             | 1                       | 0                      |         |
| (iii) Participant choice/ other reasons               | 7 (11)                  | 4 (6)                  | 0.36    |
| unwilling to come for increased study visits          | 1                       | 1                      |         |
| relocated                                             | 1                       | 1                      |         |
| stopped taking study medication                       | 1                       | 0                      |         |
| changed mind following baseline visit                 | 2                       | 0                      |         |
| commenced on immunosuppressant                        | 1                       | 0                      |         |

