## EXPERIMENTAL DESIGN AND METHODS

### Protocol

**Subjects** (n=150, to give n=120 complete) will be aged 2 to 15 years with CKD stages 1-4 in the last 12 months. Subjects will be eligible to enter the study whilst on anti-hypertensive/s medications irrespective of recent change/s in anti-hypertensive therapy. Detailed inclusion and exclusion criteria are described later in this document under 'Section 3'. Subjects with arterio-venous fistulae, on dialysis or those with a previous kidney transplant at the time of study entry will be excluded. eGFR will be

calculated using the Schwartz formula and CKD staged as per existing definitions [31,32]. Patients who reach end stage renal failure and commence dialysis or receive a kidney transplant will stop participating in the 'randomised controlled trial' but continue to have measurements performed until the end of the study. Informed consent/assent will be obtained from parents and patients (if age applicable) for participation in the study, as per institutional ethics committee approval. A control group (n=120) of age matched children without CKD will be included with all proposed study related investigations to be performed at baseline and at annual intervals. These will be recruited from siblings of study subjects and from a local community using links from a school based liaison project. In addition we aim to recruit a further control group (n=30) of subjects with systolic BP <50th percentile but on no anti-hypertensive medication.

All study related investigations at 'baseline' will be performed just before randomisation. Following enrolment and performance of baseline investigations children with CKD will be randomised to the two arms of the study: aggressive BP control (below the 40th percentile) or standard BP control (between 50th-75th percentile). A minimisation procedure will be used to ensure that patients randomised to the two arms are matched for: age, gender, CKD stage and proteinuria. Children will be recruited over the first 12-months of the study and will therefore have at least 2-years of follow up. Following randomisation all children in whom blood pressure is not to target will be reviewed at 2-4 weekly intervals. Thereafter all children will be monitored at least 4-monthly at the time of routine hospital visits and have clinic BP maintained in the assigned target range over the duration of the study.

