## **3. Data analysis plan – Inferential analysis**

Analysis will be completed according to an intention to treat principle.

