#### **3.1.1 Model assumptions**

Mixed effect models will assume a linear change in outcome over time.

It will be assumed that there is no difference between treatment arms at baseline (as confirmed by baseline comparability (Section 2.1).

Missing data from loss to follow-up/withdrawal will be assumed missing at random.

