### **3.1.4 Sensitivity analyses**

Sensitivity analyses relaxing the assumptions of a linear change in outcome over time will be completed.

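### Children withdrawn for ACEi/ARB adverse effects are not kept under outcome measurement, and no planned analysis tests the missing-at-random assumption on which the intention-to-treat result then rests

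*Combined protocol and SAP*

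**What the plan says.** - **Withdrawal rule.** SAP 1.3, Patient withdrawal, item (i): "Subjects will be withdrawn if they are unable to tolerate the performance of study related measurements or if they develop concerning adverse effects". The effects meant are those of the ACEi/ARB class. Protocol 3.3(i) has the same rule. SAP 1.4 makes this class the required first-line treatment and adjusts its dose towards the assigned target.
- **Data after withdrawal.** Item (i) does not say whether echocardiography continues. Item (ii), on families who choose to leave, does: "No further data or tissue would be collected or any other research procedures carried out on or in relation to the participant".
- **A contrasting provision.** Under Experimental Design and Methods, the protocol says that children who reach end-stage renal failure and start dialysis or are transplanted leave the randomised trial "but continue to have measurements performed until the end of the study".
- **What happened.** Table S3, headed "Details of reasons for stopping further follow up of eligible randomly assigned study participants", has a row for ACEi/ARB intolerance.
- **Analysis.** SAP 3: "Analysis will be completed according to an intention to treat principle". SAP 3.1.1: "Missing data from loss to follow-up/withdrawal will be assumed missing at random". SAP 3.1.4: "Sensitivity analyses relaxing the assumptions of a linear change in outcome over time will be completed". Protocol 2.4 adds sensitivity models with further prognostic variables. SAP 2.2 only counts withdrawals and describes the reasons.

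**The concern.** An intention-to-treat comparison of two blood pressure targets needs LV mass index (LVMI) on every randomised child, including those who could not stay on the strategy. Once measurement stops with treatment, later LVMI is unobserved for children whose departure was caused by treatment. The mixed model then fills the gap implicitly, predicting each child's later course from earlier values and from children in the same arm who were still observed. If LVMI drifts back after the strategy is abandoned, that prediction is too favourable. The estimate then moves towards the effect of the strategy while it is followed, and away from the effect of assigning it.

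Two features make the assumption worth testing. Allocation is open-label (SAP 1.5), so whoever judges an adverse effect to be concerning knows the arm. Also, 5 of the 6 intensive-arm and 2 of the 3 standard-arm intolerance stops were for reduced glomerular function. The protocol background cites a European paediatric CKD trial in which LV hypertrophy was associated with reduced GFR, yet SAP 3.1 names no on-study GFR in the model. Missingness may therefore depend on something related to the outcome and outside the model.

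**Working it through.** **1. Table S3 reproduces.** The rows add up: 2+6+7+3 = 18 (intensive, n=64) and 0+3+4+3 = 10 (standard, n=60). Uncorrected chi-square tests and Newcombe 95% intervals give:

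| Stops | Intensive | Standard | Difference, points (95% CI) | p (stated) |
|---|---|---|---|---|
| All | 18/64 = 28.1% | 10/60 = 16.7% | 11.5 (-3.4 to 25.5) | 0.127 (0.13) |
| ACEi/ARB intolerance | 6/64 = 9.4% | 3/60 = 5.0% | 4.4 (-5.7 to 14.5) | 0.348 (0.36) |
| Target not reached | 2/64 = 3.1% | 0/60 | 3.1 (-3.3 to 10.7) | 0.167 (none) |
| eGFR <15 | 3/64 = 4.7% | 3/60 = 5.0% | -0.3 (-9.5 to 8.5) | 0.935 (0.94) |

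The direction is as expected overall and for intolerance, but every interval includes zero.

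**2. Does the rule end measurement?** Item (i) is silent. The only written bar on further data is in item (ii). Table S3 supplies the practice: it counts intolerance among the reasons for ending follow-up.

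**3. Is missing at random tested?** SAP 3.1.4 relaxes linearity. The protocol 2.4 sensitivity analyses add covariates, which can make the assumption more plausible but still rely on it. Neither asks what happens if unobserved values are worse than predicted.

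**4. Size if the assumption fails.** Let f be the fraction of an arm that stopped. Let δ be the mean unobserved change in LVMI minus the model's prediction (positive means worse). The benefit is overstated by

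f_I × δ_I − f_S × δ_S.

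The documents give no δ, so the values are assumptions. δ = 3.1 g/m^2.7 in the intensive arm only means that those children lose the whole planned benefit. Entries are in g/m^2.7, for δ in the intensive arm only (same δ in both arms in brackets):

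| Stops counted | f_I, f_S | δ = 1 | δ = 3.1 | δ = 6 |
|---|---|---|---|---|
| Intolerance (the rule itself) | 6/64, 3/60 | 0.09 (0.04) | 0.29 (0.14) | 0.56 (0.26) |
| Plus target failure and eGFR <15 | 11/64, 6/60 | 0.17 (0.07) | 0.53 (0.22) | 1.03 (0.43) |
| All stops | 18/64, 10/60 | 0.28 (0.11) | 0.87 (0.36) | 1.69 (0.69) |

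For the rule itself: 6/64 = 0.094; 0.094 × 3.1 = 0.29; 0.29/3.1 = 9%. With the two other reasons: 11/64 = 0.172; 0.172 × 3.1 = 0.53; 0.53/3.1 = 17%.

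The 3.1 (SAP 1.8) serves only as a yardstick. With SD 6 and 60 per group, the standard error is 6 × √(2/60) = 1.095, and two-sided power is Φ(3.1/1.095 − 1.96) = 80.8%, not the stated 90%. That is a separate matter and nothing here depends on it.

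**The case against.** The strongest reply is that a mixed model does not discard withdrawn children. It uses all their data up to departure, and unequal withdrawal is compatible with missing at random. Bias needs unobserved LVMI to differ from the prediction, and nothing in the documents shows that it does. This stands. It limits the point to an untested assumption, and it is why the figures above are ceilings for a given δ.

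Four stronger readings are tempting and not supported:

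- **Table S3 proves that the lower target drives children out.** A 4.4-point difference with an interval from -5.7 to 14.5 does not show that. It is a reasonable expectation from the design.
- **The bias from the rule is 0.53.** That figure adds target failure and eGFR <15, which item (i) does not name. The eGFR row is balanced at 3 v 3.
- **Table S3 contradicts the protocol on end-stage disease.** The protocol provision concerns children who start dialysis or are transplanted, whereas the table row is eGFR <15. A child could also leave the trial and still be measured in the wider study. This is an ambiguity, not a proven breach.
- **The plan forbids further data after an adverse-effect withdrawal.** That sentence is in item (ii). For item (i), the loss of follow-up is inferred from the results table.

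**Conclusion.** The gap is real and moderate. The withdrawal rule ties the end of participation to a treatment adverse effect without preserving outcome measurement, Table S3 shows that follow-up ended for this reason in 6/64 v 3/60, and the promised intention-to-treat analysis depends on an assumption that no planned analysis probes.

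On the rule alone, the overstatement is at most about 0.29 g/m^2.7 (9% of 3.1), assuming that every intensive-arm child withdrawn under it lost the full two-year benefit and that the model predicted none of that loss. Counting target failure and eGFR <15 raises the ceiling to 0.53 (17%) on the same assumption. A deterioration beyond loss of benefit would give more, and a similar departure in both arms would give less. The documents fix neither the size nor the sign of δ, so none of these is an estimate of bias in this trial.

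**What to change.** 1. **Protocol 3.3(i) and SAP 1.3(i):** state that a child who stops trial-related treatment stays on the annual echocardiography schedule unless the child or family withdraws consent to follow-up. Record the two events separately.
2. **SAP 3:** state that measurements after treatment discontinuation enter the intention-to-treat model.
3. **SAP 3.1.4:** add an analysis for outcomes still missing, either delta-adjusted by arm over a stated range of δ or reference-based, with intensive-arm values imputed from the standard arm.
4. **Reconcile** the protocol's provision for continued measurement after dialysis or transplant with the eGFR <15 row of Table S3, and say whether those later measurements belong to the trial analysis.

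The cost is some continued visits for children no longer on the strategy, on a schedule that the flowchart already contains, and a little extra analysis. The documents do not say how visits are funded. Since Table S3 and Figure S6 report follow-up to date, item 3 is the part that can still inform this trial's result once follow-up has closed. No rule for stopping treatment changes.
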